### Sample size

Sample size was initially estimated using a repeated-measures ANOVA framework as an approximation of the planned longitudinal analysis, implemented in G*Power software (version 3.1.9.6). A small effect size was assumed (f = 0.10), consistent with meta-analytic evidence from self-determination theory–based interventions (g ≈ 0.40) [14] and body image programs (g ≈ 0.40) [19].

With a significance level of α = 0.05 and statistical power (1 − β) of 0.80, and assuming two groups with three repeated measurements, the minimum required sample size was estimated to be 164 participants (82 per group). To account for an anticipated attrition rate of approximately 20%, the target sample size was increased to 196 participants.

Given the longitudinal design of the study and the use of mixed models for repeated measures (MMRM) as the primary analytical approach, simulation-based power analyses were subsequently conducted in R to obtain more realistic estimates under plausible assumptions.

These simulations incorporated baseline adjustment, within-subject correlation, and missing data patterns consistent with behavioral interventions. Effect sizes were specified in the small-to-moderate range (d ≈ 0.20–0.30), and assumptions regarding residual variability and within-subject correlation were informed by prior literature on autonomous motivation (RAI).

Power was evaluated with respect to the primary contrast at six-month follow-up time point.

Simulation results indicated that the planned sample size provides moderate, and in some scenarios approaching adequate, statistical power under realistic assumptions, while reflecting the inherent variability associated with behavioral and psychological outcomes.

These complementary approaches ensured both consistency with conventional sample size estimation methods and alignment with the planned analytical model.

To account for potential deviations from the target sample size, contingency strategies were pre-specified. If the final sample exceeds the planned size, all participants will be retained in the analyses to maximize statistical power and precision. If the achieved sample size falls below the target, additional recruitment efforts will be undertaken following the same procedures. Based on the initial assumptions, a minimum sample size of 70 participants per group would still provide adequate statistical power (1 − β = 0.80) to detect moderate effects (g ≈ 0.40).

Detailed simulation parameters are provided in the Statistical Analysis Plan.

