An appropriate covariance structure (e.g., unstructured or alternative based on model fit indices) will be specified to account for within-participant correlations across repeated measurements. The primary endpoint will be the between-group difference at six-month follow-up, while effects at post-intervention will be considered secondary analyses. Least-squares mean differences between groups will be estimated from the model, along with corresponding 95% confidence intervals and p-values. This likelihood-based approach uses all available observed data without imputing missing values and provides valid inferences under the missing at random (MAR) assumption. Secondary outcomes, including satisfaction and frustration of basic psychological needs, physical activity levels, positive body image, and risk of eating disorders, will be analyzed using equivalent MMRM approaches. In cases where parametric assumptions are violated, robust mixed-effects models and bootstrapping procedures will be applied to obtain reliable parameter estimates. Exploratory analyses of the six BREQ‑3 subscales will follow the same mixed‑effects modelling approach. In addition, mediation will be tested with a half-longitudinal model [34]: group is the independent variable, the change in autonomous motivation (BREQ-3 RAI) from T0 to T1 is the mediator, and the changes in physical activity (IPAQ-SF), positive body image (BAS-2), and eating disorder risk (EAT-26) from T1 to T2 are the outcomes. The primary specification is a single-level structural equation model (lavaan) with bias-corrected bootstrap confidence intervals for the indirect effect; a multilevel SEM that accounts for the partially nested delivery subgroups is reported as a sensitivity analysis. Full detail is given in the SAP (see Supporting information S3 File). Statistical significance will be set at p < .05. Effect sizes will be calculated to facilitate interpretation of the magnitude of effects. Ninety-five percent confidence intervals will be reported for all relevant estimates.

To enhance transparency and reproducibility, a complete Statistical Analysis Plan (SAP, v2.0), structured following the template by [35], is provided as supplementary material (S3 File).

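### The 0.80 power behind N = 164 belongs to an omnibus ANOVA at a difference of about 0.42–0.49 SD; it is not power for a small effect on the six-month contrast

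*Protocol article*

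**What the plan says.** All of the power material is in the protocol article, section Sample size. It opens: "Sample size was initially estimated using a repeated-measures ANOVA framework as an approximation of the planned longitudinal analysis". The effect size follows: "A small effect size was assumed (f = 0.10), consistent with meta-analytic evidence from self-determination theory–based interventions (g ≈ 0.40"), with a similar g cited for body image programmes. For two groups measured three times, at α = 0.05 and power 0.80, the result is that "the minimum required sample size was estimated to be 164 participants (82 per group"). For losses, "To account for an anticipated attrition rate of approximately 20%, the target sample size was increased to 196 participants".

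The section then describes simulations for the mixed model, aimed at the T2 contrast: "Effect sizes were specified in the small-to-moderate range (d ≈ 0.20–0.30"). Their outcome is given without a number: "Simulation results indicated that the planned sample size provides moderate, and in some scenarios approaching adequate, statistical power under realistic assumptions". Simulation parameters are left to the SAP. The section ends by printing 0.80 a second time, for 70 participants per group at g ≈ 0.40, and says that this rests on the assumptions made at the outset.

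The section Statistical analysis fixes the test that decides the trial: "The primary endpoint will be the between-group difference at six-month follow-up", estimated from a mixed model with the baseline value as a covariate.

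**The concern.** The sample size is tied to one test and the trial is decided by another. An omnibus interaction over three waves responds to any departure from parallel profiles, including an effect at T1 that has gone by T2. It is therefore a loose stand-in for a single contrast at T2.

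The effect scales also differ. An f of 0.10 is conventionally called small, but on the interaction scale it is a group difference near 0.4 SD, which is larger than the 0.20 to 0.30 used in the simulations. A reader who sees 0.80, small effect and 164 together may take it that the primary test has 80% power for a small effect. If so, a non-significant T2 result would be given more weight against a small effect than it can carry.

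**Working it through.** **Inputs from the article.** Two groups, three waves, α = 0.05, f = 0.10, power 0.80, N = 164; target 196 in a 1:1 ratio; about 20% attrition; d = 0.20 to 0.30 in the simulations; g ≈ 0.40 from the cited meta-analyses; baseline-adjusted T2 contrast as primary.

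**Assumed, because the article does not give them.** Correlation among waves ρ = 0.5 and sphericity 1 for the ANOVA; a two-sided test; baseline-to-T2 correlation r, shown from 0 to 0.8.

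**1. Reproducing 164.** Within-between interaction: λ = f²·N·m/(1 − ρ), with df 2 and 2(N − 2).
- N = 164: λ = 0.01 × 164 × 3/0.5 = 9.84, df 2 and 324, critical F 3.02, power 0.805.
- N = 162: power 0.7998, just short, so 164 is the minimum with equal groups.
- The within-factor (time) test gives the same N. The between-group test would need 526, so 164 is not a between-group calculation.

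**2. What f = 0.10 means as a group difference.** For group differences δ at T0, T1 and T2, the interaction f is √(population variance of δ / 4).
- Pattern (0, d, d): √((2/9)/4)·d = 0.2357d, so f = 0.10 gives d = 0.42.
- Linear pattern (0, d/2, d): √((1/6)/4)·d = 0.2041d, so d = 0.49.
- Pattern (0, d, 0) has the same variance as (0, d, d). An effect of 0.42 SD at T1 and nothing at T2 therefore also meets f = 0.10.

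**3. Power of the T2 contrast.** Analysed per arm: 196 × 0.8 / 2 = 78.4, taken as n = 78. In SD units SE = √(2(1 − r²)/n), and power ≈ Φ(d/SE − 1.96). At r = 0.5, SE = √(2 × 0.75/78) = 0.139. The table gives the noncentral t value, with this normal approximation in brackets.

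| r | d = 0.20 | d = 0.30 | g = 0.40 |
|---|---|---|---|
| 0 | 0.237 (0.239) | 0.461 (0.466) | 0.699 (0.705) |
| 0.3 | 0.256 (0.258) | 0.497 (0.502) | 0.740 (0.745) |
| 0.5 | 0.300 (0.303) | 0.575 (0.581) | 0.818 (0.822) |
| 0.7 | 0.412 (0.417) | 0.741 (0.746) | 0.935 (0.938) |
| 0.8 | 0.543 (0.548) | 0.873 (0.877) | 0.985 (0.986) |

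A mixed-model information calculation with 98 randomised per arm, and an assumed 10% missing at T1 and 20% at T2, gives 0.31 and 0.59 at r = 0.5 for d = 0.20 and 0.30. Borrowing from T1 changes little.

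**4. Effect detectable with 0.80 power at 78 per arm.** (1.96 + 0.84) × SE is 2.80 × 0.139 = 0.39 SD at r = 0.5, and 2.80 × 0.114 = 0.32 SD at r = 0.7. Neither allows for clustering within the workshop subgroups.

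**5. The second 0.80 (70 per group).** Under the initial ANOVA assumptions with N = 140, λ = 0.01 × 140 × 3/0.5 = 8.40 and power is 0.73. Reading g ≈ 0.40 as f = 0.20 in the same test gives power above 0.99. As a T2 contrast at g = 0.40 with 70 analysed per arm, power is 0.65 at r = 0, 0.77 at r = 0.5 and 0.84 at r = 0.6. The figure is thus roughly right as a baseline-adjusted contrast, but not on the basis that the article names.

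**The case against.** The article is more candid than a quick reading suggests. It says that the T2 contrast was simulated at cautious effects, it claims only moderate power there, and it sends the parameters to the SAP, which is not at hand. It would be wrong to infer that the primary contrast was never examined, or that the simulations are missing.

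The article also ties f = 0.10 to g ≈ 0.40, which agrees with the 0.42 SD above; only the label small misleads. At g ≈ 0.40 the T2 contrast does reach about 0.82 with r = 0.5, so the documents do not support calling the trial underpowered for the effect that its cited evidence suggests.

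A reader might also infer that the article claims its two approaches agree on the effect size. It does not: it claims consistency with conventional methods and alignment with the planned model. Nor is the ANOVA figure the only 0.80 in print, and its test family is inferred, since the time test gives the same 164.

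The range 0.30 to 0.58 cannot be quoted alone, because it needs r = 0.5. The section Primary outcome cites high temporal stability of the scale, which leans towards a higher r; at r = 0.8 and d = 0.30 power is about 0.87. Finally, a null result would not be empty: at r = 0.5 the 95% interval has a half-width of 1.96 × 0.139 = 0.27 SD, so an estimate near zero would exclude 0.30, though not 0.20.

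All of this narrows the point. It does not remove it: the printed 0.80 sits beside the word small, and no number is printed at the effects that the plan treats as realistic.

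**Conclusion.** The point stands in a limited form. The 0.80 attached to 164 describes an omnibus three-wave test at a difference of about 0.42 to 0.49 SD. It is not power for a small effect on the primary T2 contrast. For d = 0.20 to 0.30 with 78 analysed per arm, power is about 0.26 to 0.50 (r = 0.3), 0.30 to 0.58 (r = 0.5), 0.41 to 0.74 (r = 0.7) and 0.54 to 0.87 (r = 0.8). It reaches 0.80 only near d = 0.30 with r of about 0.75 or more, and at d = 0.20 it stays below 0.80 throughout this range. The article's verbal summary is fair for the upper effect and generous for the lower one. The second 0.80 needs a different basis from the one stated.

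These figures assume a two-sided 0.05 test, 20% loss in each arm and no clustering. The unknown r is the main source of spread.

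**What to change.** In the section Sample size, with no change to enrolment:

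- State that 0.80 applies to a group difference of about 0.4 SD, and remove small as the description of what 164 detects.
- Label 164 as coming from the omnibus repeated-measures ANOVA, naming the test family and the correlation used.
- Beside it, print the simulated power for the T2 contrast at d = 0.20 and 0.30 with the baseline-to-T2 correlation assumed, and the effect detectable at 0.80. On the figures here that is about 0.39 SD at r = 0.5 and 0.32 SD at r = 0.7, before clustering. The full simulation settings can stay in the SAP.
- Restate the 70-per-group figure as a baseline-adjusted T2 contrast at g ≈ 0.40 with its correlation, or withdraw the statement that it follows from the initial assumptions.

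The cost is a few sentences and a stated power that looks less favourable. The article reports that recruitment has not begun, so the change can be made before any data exist.

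### A target of 196 does not preserve the minimum of 164 at 20% attrition: it leaves about 157 completers and covers only about 16% loss (minor, wrong as written)

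*Protocol article*

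**What the plan says.** The Sample size section of the protocol article works in two stages.

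The first stage is a conventional calculation: "Sample size was initially estimated using a repeated-measures ANOVA framework as an approximation of the planned longitudinal analysis". It takes an effect size f of 0.10. The remaining inputs are given as "With a significance level of α = 0.05 and statistical power (1 − β) of 0.80" and "assuming two groups with three repeated measurements". The result is that "the minimum required sample size was estimated to be 164 participants (82 per group"). The attrition step follows directly: "To account for an anticipated attrition rate of approximately 20%, the target sample size was increased to 196 participants". No inflation formula is printed.

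The second stage is a set of simulations for the planned MMRM, which include missing data and evaluate the six-month contrast. They are summarised as giving moderate power, coming close to adequate in some scenarios. The target stays at 196.

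The section closes with contingencies: further recruitment if the achieved sample falls short of the target, and a fallback of 70 per group for an effect g of about 0.40. The section on randomization specifies 1:1 allocation.

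**The concern.** An attrition allowance should ensure that the required number remains after the expected loss. The required number is 164, the expected loss is about 20%, and the target is said to account for that loss. If 196 enrolled participants lose 20%, fewer than 164 remain, so the target lacks the property claimed for it.

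At stake is the accuracy of the enrolment figure on which the trial relies. The recruitment contingency is also tied to that figure. A team that enrolled exactly 196 and then lost the 20% it expected would end below its own minimum, and the contingency as worded would not be triggered, since the target would have been met.

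**Working it through.** **Inputs from the Sample size section:** minimum 164 (82 per group); attrition 20%; target 196; f = 0.10; α = 0.05; power 0.80; 2 groups; m = 3 measurements. **From the randomization section:** 1:1 allocation.

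**Assumed, because the article does not state them:** the tested effect is the within-between interaction, the correlation between measurements is ρ = 0.5, and the sphericity factor is ε = 1.

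**Step 1. Reproduce 164.** For this F test the noncentrality is λ = f² · N · m / (1 − ρ), with 2 and 2(N − 2) degrees of freedom.
- N = 164: λ = 0.01 × 164 × 3 / 0.5 = 9.84, df 2 and 324, power 0.805.
- N = 162: power 0.7998, just under 0.80.

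So 164 is the smallest even N that reaches 0.80, an exact match. With two groups, the test of the within-subject factor gives the same N. The between-group test would need 526. The interaction calculation is sensitive to ρ: the required N is 228 at ρ = 0.3 and 98 at ρ = 0.7. The match at ρ = 0.5 is therefore good evidence of what was used, though not proof.

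**Step 2. Reproduce 196.**
- Multiplying: 164 × 1.2 = 196.8. Per group, 82 × 1.2 = 98.4; rounded down, 2 × 98 = 196.
- Dividing: 164 / (1 − 0.20) = 205. Per group, 82 / 0.80 = 102.5; rounded up, 2 × 103 = 206.

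The printed figure agrees with the first form and not with the second.

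**Step 3. What 196 delivers.**
- At 20% loss: 196 × 0.80 = 156.8, about 157 in total and 98 × 0.80 = 78.4 per group.
- Shortfall against the minimum: 164 − 157 = 7.
- Largest loss that still leaves 164: 1 − 164/196 = 16.3%.

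This step uses only printed numbers and holds whichever formula produced 196.

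**Step 4. Effect on power, on the assumptions of Step 1.**

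| Enrolled | Completers at 20% loss | ANOVA-based power |
|---|---|---|
| 196 | about 157 (λ = 9.42, df 2 and 310) | 0.786 |
| 206 | 206 × 0.80 = 164.8, about 165 | about 0.81 |

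The like-for-like difference between the two targets is about 2 percentage points.

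**The case against.** The strongest objection is that little depends on this. The 0.80 belongs to a calculation that the protocol itself presents as a preliminary approximation. The later simulations address the actual model and the six-month contrast with missing data included, and they already describe power as short of adequate or only close to it. That stands. A reader might infer that the attrition step costs the trial its 0.80 power for the primary analysis. The article does not support that reading, because it does not claim 0.80 for that analysis, and a corrected allowance would not change the simulation summary.

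A reader might also set power at N = 206, which is 0.890, against 0.786 at 157 and see a gain of about 10 points. That compares 206 completers with no attrition against 157 after attrition. With no attrition, 196 itself gives 0.874.

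It is tempting to state as fact that a factor of 1.2 was applied. The match is close but needs rounding down, and no formula is printed, so this remains an inference.

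Other defences are weaker:
- The word approximately gives some room, but it would have to stretch from 20% to 16.3%.
- The MMRM uses partial data, but a participant lost before T2 has no observation at the primary time point. Her T1 value recovers only part of the information. The step from 164 to 196 is in any case made within the ANOVA calculation.
- The 70-per-group fallback is a second stated minimum, and 78 per group exceeds it. However, it is a separate statement for g of about 0.40, and the 20% allowance is applied to 164.
- The analysis plan is not shown, but this is a conflict between printed figures, not a detail left to that plan.

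**Conclusion.** The point holds as a minor error in what is written. The target of 196 does not account for about 20% attrition from a minimum of 164: it leaves about 157 completers, 7 too few, and covers about 16%. That conclusion needs no assumption beyond the printed figures.

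The size in power terms is about 2 points, from 0.805 to 0.786. It rests on the unstated interaction test, ρ = 0.5 and ε = 1, and applies only to the initial ANOVA calculation. No design feature, estimand or planned analysis is affected.

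**What to change.** Rewrite the attrition sentence in one of two ways:
- state that 196 allows for about 16% attrition from the minimum of 164; or
- keep 20% and state that it would leave about 157 completers, with ANOVA-based power of about 0.79 (giving the correlation and sphericity values used).

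Either costs one sentence and no extra participants; the second makes the stated power slightly less favourable. If the team wishes to keep both 20% and 0.80 on the initial calculation, the target becomes 206 (103 per group), which is 10 more participants and about 0.81 power after the expected loss. The timeline section says recruitment has not begun, so any of these can be settled beforehand.

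### The statement that 70 per group still gives 0.80 power at g ≈ 0.40 does not follow from the initial assumptions it cites

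*Protocol article*

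**What the plan says.** All of this stands in the protocol article, Sample size.

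- The framework: "Sample size was initially estimated using a repeated-measures ANOVA framework as an approximation of the planned longitudinal analysis".
- The effect: "A small effect size was assumed (f = 0.10), consistent with meta-analytic evidence from self-determination theory–based interventions (g ≈ 0.40"). The same g is cited for body image programs.
- The design inputs: "With a significance level of α = 0.05 and statistical power (1 − β) of 0.80, and assuming two groups with three repeated measurements".
- The result: "the minimum required sample size was estimated to be 164 participants (82 per group"). The target is then raised to 196 for about 20% attrition.
- Simulations for the planned mixed model followed, at d of about 0.20 to 0.30. Of these the section says: "Power was evaluated with respect to the primary contrast at six-month follow-up time point". It describes power at the planned size as moderate, in some scenarios approaching adequate.
- The contingency paragraph says that a shortfall against the target leads to further recruitment. It closes by stating that, on the initial assumptions, "a minimum sample size of 70 participants per group would still provide adequate statistical power", given as 0.80, for effects it calls moderate (g ≈ 0.40).

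Under Statistical analysis, the primary endpoint is the group difference at six months, from a model with the baseline value as a covariate.

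**The concern.** One section gives two minimum sizes for 0.80 power, 82 and 70 per group. It refers both to the same initial assumptions and mentions g ≈ 0.40 in connection with both. A reader cannot tell which effect, which test or which correlation lies behind the 70.

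The sentence is the only statement in the article of what an under-recruited trial could still detect. If the figure has no derivation, it could later be cited to describe a smaller trial as adequately powered, and so to read more into a null result than the data allow.

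**Working it through.** **Inputs.** From Sample size: α = 0.05, power 0.80, k = 2 groups, m = 3 measurements, f = 0.10, stated N = 164, fallback 70 per group (N = 140), g ≈ 0.40. From Randomization, blinding, and allocation: ratio 1:1. Assumed, because the article states neither: within-subject correlation r = 0.5 and sphericity (ε = 1).

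**Step 1. Reproduce 164.** For the repeated-measures ANOVA within-between interaction, λ = f²·N·m·ε/(1 − r), df1 = (k − 1)(m − 1)ε and df2 = (N − k)(m − 1)ε.

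- N = 164: λ = 0.01 × 164 × 3 / 0.5 = 9.84, df = 2 and 324, power 0.805.
- N = 162: λ = 9.72, power just under 0.80.

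So 164 is exactly the minimum under these inputs.

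**Step 2. Same calculation at 70 per group, g read as f = 0.10** (the article's own equation of the two).

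- N = 140: λ = 0.01 × 140 × 3 / 0.5 = 8.40, df = 2 and 276, power 0.735.
- Raising r to 0.6 lifts this to 0.83, but the minimum for f = 0.10 then becomes 130, and 164 is no longer reproduced.

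**Step 3. Same calculation, g converted conventionally.** For two equal groups f = d/2, so g = 0.40 is f = 0.20, and f = 0.10 is d = 0.20.

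- Minimum N is 42: λ = 0.04 × 42 × 3 / 0.5 = 10.08, power 0.80.
- At N = 140: λ = 33.6, power above 0.99.

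The figure 70 per group is therefore the 0.80 point under neither reading.

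**Step 4. Is there another route to 70?** The between-groups main effect over all three waves has λ = f²·N·m/(1 + (m − 1)r). At f = 0.20 and r = 0.5 it needs N = 134 and gives 0.82 at N = 140. This comes close, but the same test at f = 0.10 needs N = 526, so it is not the calculation behind 164. It also averages in the baseline wave, so it is not the six-month contrast.

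**Step 5. The primary contrast.** Two-sided noncentral t, 2n − 2 degrees of freedom, noncentrality d / √(2(1 − ρ²)/n), where ρ is the baseline-to-T2 correlation. This approximates the baseline-adjusted mixed-model contrast with n analysed per group. For d = 0.40 and n = 70:

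| ρ | Noncentrality | Power |
|---|---|---|
| 0 (unadjusted) | 2.37 | 0.65 |
| 0.3 | 2.48 | 0.69 |
| 0.5 | 2.73 | 0.77 |
| 0.55 | 2.83 | 0.80 |
| 0.6 | 2.96 | 0.84 |
| 0.7 | 3.31 | 0.91 |

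For 0.80 power at d = 0.40, the analysed number per group is 100 at ρ = 0, 75 at ρ = 0.5 and 64 at ρ = 0.6.

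For context, at d = 0.30, the top of the simulated range, 70 analysed per group give 0.42 (ρ = 0) to 0.69 (ρ = 0.7).

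**The case against.** The strongest defence is that the two minimums belong to different effects: 82 goes with a small effect (f = 0.10) and 70 with a moderate one (g ≈ 0.40). A smaller number for a larger effect is no contradiction. This stands as far as it goes. The two figures clash directly only through the article's remark that f = 0.10 is consistent with g ≈ 0.40. But it does not rescue the 70, because the larger effect in the same calculation gives 42 participants in total, not 140.

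A reader might infer that 70 per group cannot give 0.80 power at all. The article does not support that. The planned model adjusts for baseline, so the unadjusted 0.65 is not the planned analysis, and from a correlation of about 0.55 upward the stated power is reached. The article mentions high temporal stability of the scale, without a figure, and leaves simulation parameters to the statistical analysis plan.

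A reader might also infer that the shortfall rule depends on the 70. It does not. The rule is further recruitment, and it is triggered by missing the target. Nothing says that recruitment stops, or that the trial is declared adequate, at 70 per group. The open statement that power at the planned size is only moderate to nearly adequate also tempers the risk of over-reading a null result.

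Finally, one could deduct 20% attrition (70 × 0.8 = 56 per group), which gives 0.56, 0.68 and 0.75 at ρ = 0, 0.5 and 0.6. The article uses its minimum of 164 before adding attrition, so 70 most naturally means analysed participants. The 56 should not be taken as the size of the problem, although the sentence ought to say which is meant.

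**Conclusion.** The point holds in a limited form: a stated power figure does not follow from the basis it cites. On the inputs that reproduce 164, 140 participants have power 0.73 if g ≈ 0.40 is equated with f = 0.10 as the article does, and above 0.99 if it is converted to f = 0.20. Neither is 0.80. The mismatch starts with the statement equating a small f with a g twice its size.

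For the six-month contrast at d = 0.40, the claim is conditional rather than false: it fails below a baseline-to-T2 correlation of about 0.55 and holds above it.

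The first conclusion rests on r = 0.5 and sphericity, which are assumed but reproduce the article's number exactly. The second rests on 70 analysed per group and a normal-theory baseline-adjusted comparison. The target of 196, the primary analysis and the recruitment rule are not affected by this point.

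**What to change.** 1. Correct the effect-size statement: f = 0.10 corresponds to d = 0.20 for two equal groups, and g ≈ 0.40 to f = 0.20. Say which of the two the initial calculation was meant to detect, and state its within-subject correlation and sphericity assumption.
2. Delete the 70-per-group sentence, or restate it for the baseline-adjusted six-month contrast with its effect size, assumed correlation and resulting power, counting analysed participants. For example: with 70 analysed per group and d = 0.40, power is about 0.77 at a baseline-to-T2 correlation of 0.5 and 0.84 at 0.6. Drop the reference to the initial assumptions.

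The cost is a rewording of two sentences and a stated power that is less favourable or openly conditional. No design element has to change.
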